## Abstract

**Background:**

The current standard treatment for elderly patients with newly diagnosed glioblastoma is surgery followed by short-course radiotherapy with temozolomide. In recent studies, 40 Gy in 15 fractions vs. 60 Gy in 30 fractions, 34 Gy in 10 fractions vs. 60 Gy in 30 fractions, and 40 Gy in 15 fractions vs. 25 Gy in 5 fractions have been reported as non-inferior. The addition of temozolomide increased the survival benefit of radiotherapy with 40 Gy in 15 fractions. However, the optimal regimen for radiotherapy plus concomitant temozolomide remains unresolved.

**Methods:**

This multi-institutional randomized phase III trial was commenced to confirm the non-inferiority of radiotherapy comprising 25 Gy in 5 fractions with concomitant (150 mg/m^2^/day, 5 days) and adjuvant temozolomide over 40 Gy in 15 fractions with concomitant (75 mg/m^2^/day, every day from first to last day of radiation) and adjuvant temozolomide in terms of overall survival (OS) in elderly patients with newly diagnosed glioblastoma. A total of 270 patients will be accrued from 51 Japanese institutions in 4 years and follow-up will last 2 years. Patients 71 years of age or older, or 71–75 years old with resection of less than 90% of the contrast-enhanced region, will be registered and randomly assigned to each group with 1:1 allocation. The primary endpoint is OS, and the secondary endpoints are progression-free survival, frequency of adverse events, proportion of Karnofsky performance status preservation, and proportion of health-related quality of life preservation. The Japan Clinical Oncology Group Protocol Review Committee approved this study protocol in April 2020. Ethics approval was granted by the National Cancer Center Hospital Certified Review Board. Patient enrollment began in August 2020.

**Discussion:**

If the primary endpoint is met, short-course radiotherapy comprising 25 Gy in 5 fractions with concomitant and adjuvant temozolomide will be a standard of care for elderly patients with newly diagnosed glioblastoma.

**Trial registration:**

Registry number: jRCTs031200099.

Date of Registration: 27/Aug/2020. Date of First Participant Enrollment: 4/Sep/2020.

## Background

Glioblastoma is an incurable primary brain tumor with a median overall survival (OS) less than 2 years and a 5-year survival rate of 7.2–16%, and comprising 12–14.5% of primary brain tumors [1, 2]. The incidence of glioblastoma peaks among patients in their 60s to 70s and is increasing with the growth of the elderly population [1–3]. Age is associated with poor prognosis, and median OS is less than 12 months among patients over 70 years old [1]. Initial Karnofsky performance status (KPS) before treatment is lower than 70 in 36% of patients [1]. Furthermore, the progression of glioblastoma can easily decrease performance status by reducing functional and cognitive ability, particularly among elderly patients.

The present standard treatment for patients younger than 70 years old with glioblastoma is radiotherapy comprising 60 Gy in 30 fractions with concomitant and adjuvant temozolomide [4, 5]. Most clinical trials for glioblastoma have excluded elderly patients because of their poor prognosis, comorbidity and sensitivity of the aging brain to radiation [6]. Several studies of elderly patients with glioblastoma evaluating radiotherapy as 60 Gy in 30 fractions with concomitant and adjuvant temozolomide showed prolonged OS in patients with good performance status but treatment-related toxicities such as greater deterioration of mental status [6–9]. Although conventionally fractionated radiotherapy effectively prolonged survival in elderly patients with glioblastoma, low completion rates due to the long duration of treatment and declines in activities of daily living (ADL) remain concerning. Hypofractionated radiotherapy has thus been developed to preserve efficacy and decrease toxicities during treatment.

In 2017, the Canadian Cancer Clinical Trials Group (CCTG) and the European Organization for Research and Treatment of Cancer (EORTC) reported that median OS was longer with short-course radiotherapy comprising 40 Gy in 15 fractions plus concomitant (75 mg/m^2^, daily from first to last day of radiation) and adjuvant (150–200 mg/m^2^, days 1–5, every 4 weeks, 12 cycles) temozolomide than with 40 Gy in 15 fractions alone (9.3 months vs. 7.6 months), as was median progression-free survival (PFS) (5.3 months vs. 3.9 months) in elderly patients with newly diagnosed glioblastoma (CE.6) [10]. The addition of temozolomide to short-course radiotherapy did not disturb quality of life (QOL) within manageable chemotherapy-related adverse events. However, in a subgroup analysis, patients 65–70 years old benefited less from the addition of temozolomide than those 71–75 years old or 76 years old or older. In a background with fewer enrolled patients 65 to 70 years old than 71 to 75 years old, patients 65 to 70 years old with satisfactory performance status are generally treated with radiotherapy as 60 Gy in 30 fractions plus concomitant and adjuvant temozolomide. Based on these considerations, a regimen of radiotherapy as 40 Gy in 15 fractions plus temozolomide could be an appropriate standard treatment for newly diagnosed glioblastoma patients 71 years old or above.

Three other phase III trials were conducted for further hypofractionated radiotherapy in elderly patients with newly diagnosed glioblastoma. Those studies compared 40 Gy in 15 fractions vs. 60 Gy in 30 fractions [11], 34 Gy in 10 fractions vs. 60 Gy in 30 fractions [12], and 40 Gy in 15 fractions vs. 25 Gy in 5 fractions [13] and reported non-inferior results in terms of safety and efficacy for elderly patients with newly diagnosed glioblastoma (Table 1 [10–15]). However, those studies all had small sample sizes and the results have not been confirmed by other investigations, so the optimal dose and number of fractions remain unclear, particularly when administered in combination with temozolomide.

**Table 1 Tab1:** Randomized controlled trials in elderly patients with glioblastoma

Authors, publication year, study name	Age cut-off, years	Number	Intervention	mPFS, months	mOS, months	
Roa et al., 2004 [11]	≥60	47	60 Gy/30 fr	N/A	5.1	
		48	40 Gy/15 fr	N/A	5.6	
Keime-Guibert et al., 2007 [14], ANOCEF	≥70	42	Best supportive care	1.2	3.9	
		39	50 Gy/28 fr	3.4	6.7	
Wick et al., 2012 [15], NOA-08	> 65	178	60 Gy/30 fr	4.7	9.6	
		195	Dose-dense temozolomide	3.3	8.6	
Malmström et al., 2012 [12], Nordic study	> 70	100	60 Gy/30 fr	N/A	6	
		98	34 Gy/10 fr	N/A	7.5	
		93	Temozolomide	N/A	8.3	
Roa et al., 2015 [13]	≥65	50	40 Gy/15 fr	4.2	6.4	
		48	25 Gy/5 fr	4.2	7.9	
Perry et al., 2017 [10], CE.6	≥65	281	40 Gy/15 fr	3.9	7.6	
		281	40 Gy/15 fr + temozolomide	5.3	9.3	

*mPFS* median progression-free survival; *mOS* median overall survival; *fr* fractions; *N/A* not available

In August 2020, the Brain Tumor Study Group and the Radiation Therapy Study Group of the Japan Clinical Oncology Group (JCOG) started a multicenter randomized controlled phase III trial in elderly patients with newly diagnosed glioblastoma (JCOG1910, AgedGlio-PIII).

## Methods / design

### Aim

The purpose of this study was to confirm the non-inferiority of radiotherapy as 25 Gy in 5 fractions with concomitant and adjuvant temozolomide over 40 Gy in 15 fractions with concomitant and adjuvant temozolomide in terms of OS in elderly patients with newly diagnosed glioblastoma.

### Randomization

The first registration is performed by JCOG Web System to the JCOG Data Center if all eligibility criteria for the first registration are satisfied. Methylation status of the O6-methylguanine-DNA methyltransferase (MGMT) promoter region is examined using surgical specimens before the second registration. After confirming the inclusion criteria for the second registration have been met, the second registration will be made by the JCOG Web System to the JCOG Data Center. Patients will be randomized in a 1:1 ratio into either arm A (standard treatment arm: radiotherapy as 40 Gy in 15 fractions with concomitant and adjuvant temozolomide) or arm B (experimental treatment arm: radiotherapy as 25 Gy in 5 fractions with concomitant and adjuvant temozolomide) using a minimization method with a random component while balancing arms with respect to institution, extent of surgical resection (partial resection + total resection vs. biopsy), Karnofsky performance status (< 70% vs. ≥70%) and methylation status of the MGMT promoter region (methylated vs. unmethylated).

### Study setting

A multi-institutional, randomized controlled trial.

### Endpoints

The primary endpoint is OS, and secondary endpoints are PFS, frequency of adverse events (AEs), proportion of Karnofsky performance status preservation, and proportion of health-related QOL preservation.

OS is defined as the time from registration to death from any cause, censored as of the last day when the patient is known to be alive. PFS is defined as the time from registration to either the first event of tumor progression or death from any cause, censored as of the latest day when the patient is alive without any evidence of progression. Tumor response is evaluated according to the Response Assessment in Neuro-Oncology (RANO) criteria [16]. AEs are evaluated according to the Common Terminology Criteria for Adverse Events version 5.0 (CTCAE 5.0). SAE is defined as any ≥ grade 4 non-hematological toxicity at least possibly related to treatment, unexpected AE requiring hospitalization or prolongation of hospital stay, death from any cause during treatment or within 30 days after a protocol treatment, or treatment-related death. Health-related QOL is measured in accordance with EORTC QLQ-C30 and EORTC QLQ-BN20.

### Inclusion criteria

First registration criteria:
Tumor diagnosed as glioblastoma or Grade III glioma (WHO 2016 criteria) in pathological diagnosis during surgery, or histologically proven glioblastoma diagnosed according to WHO 2016 criteria.Tumor specimen available for analysis of MGMT promoter methylation status.No history of treatments for glioma except for resection including biopsy; in that case, second resection within 21 days after first resection.First registration within 21 days after surgery.Tumor present in the supratentorial region on preoperative contrast-enhanced MRI of the brain.Preoperative contrast-enhanced MRI of the brain reveals no dissemination.Presence of a measurable lesion is not mandatory.Patient 71 years old or older at registration; 71 to 75 years old with resection of less than 90% of contrast-enhanced region.ECOG performance status (PS) of 0, 1, 2, or 3 due to neurological symptoms caused by the tumor.No prior chemotherapy or radiation therapy to the brain for any intracranial tumors.Sufficient organ function.(i)Neutrophil count ≥1500 /mm^3^.(ii)Hemoglobin ≥8.0 mg/dl.(iii)Platelet count ≥100,000 /mm^3^.(iv)AST ≤ 120 U/L.(v)ALT ≤120 U/L.(vi)Cr ≤ 1.605 mg/dL for males, or ≤ 1.185 mg/dL for females.(12)Informed consent provided voluntarily by the patient.

Second registration criteria:
Second registration within 21 days of the first registration.Histologically proven glioblastoma diagnosed according to WHO 2016 criteria.Confirmation of methylation or unmethylation in MGMT promoter region.

Exclusion criteria
Synchronous or metachronous malignancies (within the preceding 2 years).Infections needing systemic treatment at time of registration.Body temperature above 38 °C at registration.Severe psychological disease at time of registration.Continuous systemic corticosteroid or immunosuppressant treatment due to diseases other than brain tumor.Uncontrollable diabetes mellitus.Unstable angina pectoris, or history of myocardial infarction within the preceding 6 months.Interstitial pneumonia, pulmonary fibrosis, or severe emphysema at time of registration.Gadolinium allergy.Positive results for HIV antibody.Positive results for HBs antigen.

### Interventions

#### Arm A:

(1) 40 Gy in 15 daily fractions with temozolomide.

(i) Concomitant phase, temozolomide (75 mg/m^2^, daily from first to last day of radiation), radiation (2.67 Gy/day, 5 days/week, 15 times and 40 Gy in total)

(ii) Maintenance phase, temozolomide (150–200 mg/m^2^, days 1–5, every 4 weeks) 12 cycles.

#### Arm B:

(1) 25 Gy in 5 daily fractions with temozolomide.

(i) Concomitant phase, temozolomide (150 mg/m^2^, 5 days from first day), radiation (5 Gy/day, 5 days/week, 5 times and 25 Gy in total)

(ii) Maintenance phase, temozolomide (150–200 mg/m^2^, days 1–5, every 4 weeks) 12 cycles.

### Procedures of radiotherapy

Contouring was performed using computed tomography (CT) with a maximum slice thickness of 5 mm. Gross tumor volume (GTV) was defined as residual tumor according to pre- and postoperative contrast-enhanced MRI. Clinical target volume (CTV) was created by adding 1.5-cm margins to the GTV and resection cavity. In addition, CTV included surrounding edema (high-intensity area on T2-weighted or fluid-attenuated inversion recovery images). The margin for the planning target volume was set at 3–5 mm. The same target setting was used for Arms A and B.

### Follow-up

All patients will be followed-up for at least 2 years after completion of protocol treatment. Gadolinium-enhanced MRI of the brain will be evaluated at least every 8 weeks until disease progression or death. Tumor response will also be assessed every 8 weeks according to RANO criteria. Physical examination, laboratory tests, and evaluation of AEs according to CTCAE version 5.0 will be carried out at least every 4 weeks during protocol treatment.

### Statistical analysis

This study is designed as a multi-institutional, randomized controlled trial to confirm the non-inferiority of radiotherapy of 25 Gy in 5 fractions with concomitant and adjuvant temozolomide over 40 Gy in 15 fractions with concomitant and adjuvant temozolomide in terms of OS in elderly patients with newly diagnosed glioblastoma. The required sample size for randomization is calculated as 264, which will provide 70% power with a hypothesized 1-year survival rate of 37.8% in both arms and a non-inferiority margin of 1.32 using a one-sided alpha of 0.05 to observe 249 deaths. Considering some patients will not be registered due to progression before the second registration, the planned sample size for the first registration is 270 patients in a 4-year accrual period and 2-year follow-up period. Stratified Cox regression analysis with extent of surgical resection, Karnofsky performance status and methylation status of the MGMT promoter region will be performed for primary analysis.

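### The primary stratified Cox model omits age, which is prognostic, already recorded and not balanced on; adding it is a cheap improvement, not the correction of an error

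*Protocol article*

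**What the plan says.** The Statistical analysis section of the protocol article names the primary model: "Stratified Cox regression analysis with extent of surgical resection, Karnofsky performance status and methylation status of the MGMT promoter region". The design is set as "a non-inferiority margin of 1.32 using a one-sided alpha of 0.05 to observe 249 deaths", with "The required sample size for randomization is calculated as 264, which will provide 70% power" and survival "with a hypothesized 1-year survival rate of 37.8% in both arms".

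The stratifiers are the minimisation factors of the Randomization section without institution. The resection factor there is "extent of surgical resection (partial resection + total resection vs. biopsy", so partial and total resection are pooled. Age appears in neither list.

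Elsewhere the article treats age as relevant. The Background says "Age is associated with poor prognosis". The Inclusion criteria admit patients from 71 years, and those aged 71 to 75 only when less than 90% of the enhancing region was resected. Age at registration is therefore known for every patient.

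**The concern.** Two things follow when a prognostic baseline variable is left out of a Cox model.

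- **Chance imbalance.** Age is not a minimisation factor, so its balance between arms rests on chance, and this model cannot correct an imbalance once it has occurred. The resection stratum cannot stand in for age. It separates biopsy from any resection, whereas the eligibility rule links age to the 90% threshold.
- **Attenuation.** The Cox HR is non-collapsible. If the true HR differs from 1, the HR from a model without age lies closer to 1 than the HR conditional on age. In a superiority trial that costs power. In a non-inferiority trial it makes an inferior arm look slightly less inferior against the margin.

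A non-inferiority claim would make the shorter regimen a standard of care (Discussion). The design has little slack, with one-sided alpha 0.05, 70% power and a margin of 1.32.

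**Working it through.** **1. The plan's own figures reproduce.** Schoenfeld events are 4(z₀.₉₅ + z₀.₇₀)²/(ln 1.32)² = 4(1.645 + 0.524)²/(0.2776)², which gives 245; Freedman's formula gives 248; the plan states 249. Power at 249 deaths is Φ(√249/2 × 0.2776 − 1.645) = Φ(0.546) = 70.7%. The hazard is −ln 0.378 = 0.973 per year. With uniform 4-year accrual and 2 further years, P(death observed) = 0.964, so 249/0.964 gives 259 patients against 264 stated. Age enters none of these figures.

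**2. How far omitting age moves the HR.** The age-conditional HR was set to 1.32 and a Cox model stratified on three binary factors was fitted without age to 1.6 million simulated patients. Age SD, age effect, stratum prevalences and stratum effects are assumptions. The rate of false non-inferiority against an age-conditional 1.32 is Φ(−1.645 + [ln 1.32 − ln HR*]/SE), where HR* is the HR without age and SE = 2/√249 = 0.1267.

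| Age HR per 10 years | HR*, SD 3.7 y | Rate | HR*, SD 4.9 y | Rate |
|---|---|---|---|---|
| 1.3 | 1.316 | 5.2% | 1.315 | 5.3% |
| 1.6 | 1.311 | 5.6% | 1.306 | 5.9% |
| 2.0 | 1.303 | 6.1% | 1.295 | 6.8% |
| 3.0 | 1.287 | 7.5% | 1.273 | 8.7% |

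Example: for HR* = 1.3031, ln(1.32/1.3031) = 0.0129; 0.0129/0.1267 = 0.102; Φ(−1.543) = 6.1%.

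**3. Trial-size simulation, with and without age.** 264 patients, eight strata, assumed log-HR per SD of age:

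| Log-HR per SD | Without age | With age |
|---|---|---|
| 0.10 | 5.6% | 5.5% |
| 0.20 | 5.4% | 4.6% |
| 0.35 | 6.9% | 5.0% |

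The entries are false non-inferiority at an age-conditional HR of 1.32. The lack of a steady trend in the first two rows is simulation noise. Power at HR = 1 was about 67% without age and 65 to 67% with it. It falls below 70.7% under either model because splitting into eight strata raises the standard error to about 0.135.

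To compare the scales: 0.2 per SD is exp(0.2 × 10/3.7) = 1.72 per 10 years at SD 3.7, or exp(0.2 × 10/4.9) = 1.50 at SD 4.9. The value 0.35 corresponds to 2.58 or 2.04.

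**4. Chance imbalance.** With 132 per arm, the difference in mean age has standard error √(2/132) = 0.123 SD. An imbalance of two standard errors, 0.246 SD, moves the log-HR by 0.246 × 0.2 = 0.049 or 0.246 × 0.35 = 0.086. That is 18% or 31% of ln 1.32 = 0.278.

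In simulated trials where arm B was younger by more than 0.15 SD, false non-inferiority was 5.6, 8.3 and 14.2% without age for the three effects above, and about 4 to 5% with age. Such trials are about one in nine under simple randomisation (0.15/0.123 = 1.22; upper tail 0.11). These conditional rates come from a small share of the runs and are less precise. An older arm B shifts the result the other way.

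**The case against.** A reader might infer that the non-inferiority test as planned is anticonservative, with an error rate of 7% or even 9.6% (the figure under an assumed 0.5 per SD). The documents do not support this, for three reasons.

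- **The margin is not defined as age-conditional.** The Statistical analysis section gives 1.32 beside an overall 1-year survival figure. The model estimates the HR conditional on resection, KPS and MGMT status, and for that HR the test keeps its 5% level. By the stronger argument every Cox non-inferiority test would be invalid, since each omits some prognostic factor. This objection stands.
- **No age effect within the enrolled range is given.** The Background statement on age is general. Taking an SD of about 4 years, 0.5 per SD means exp(0.5 × 10/4) = 3.5 per 10 years, on top of three stratifiers. The eligibility rule may also weaken the age gradient: patients aged 71 to 75 with the most complete resections are excluded, while older ones are not. This stands against the large figures, though not against a modest effect.
- **Randomisation already covers chance imbalance.** Over all possible allocations this is true, and age is not systematically imbalanced. It does not help to interpret the one allocation that is realised, and an adjustment chosen after seeing an imbalance would be open to challenge.

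The planned model is also coherent, since it uses the minimisation factors other than institution. A supportive age-adjusted analysis may well sit in the full protocol or analysis plan, and its absence from an article is no finding. What can be discussed is the primary model, which the article does fix.

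**Conclusion.** The plan contains no error or contradiction here, and its design figures reproduce. The point is an optional improvement to the primary model. Leaving age out forgoes correction of chance imbalance in a prognostic variable that is already recorded, and it shifts a non-null HR slightly in the unfavourable direction.

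For assumed age effects of 0.1 to 0.35 in log-HR per SD, false non-inferiority against an age-conditional HR of 1.32 is about 5.5 to 7% without age and about 5% with it. At true HR = 1 there is no attenuation and power is essentially the same. Higher rates need strong age effects that the documents do not support, or apply only to realised trials in which arm B happens to be younger. All these sizes rest on assumed age distributions and age effects, and they count as inflation only if the margin is read as conditional on age.

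**What to change.** Before unblinding, add one sentence to the Statistical analysis section: the primary Cox model stays stratified by extent of resection, KPS and MGMT status and includes age at registration as a continuous covariate. The model without age is reported as a sensitivity analysis. Since an interim analysis for efficacy and futility is planned, the change is best fixed before comparative survival results are seen.

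The cost is one more pre-specified term and a power change of at most about 1 to 2 points. No new data are needed and the sample size does not change. The reported HR then becomes conditional on age as well as on the three strata, and the text should say that the 1.32 margin is applied to that HR.

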### Interim analysis and monitoring

We plan to conduct an interim analysis to judge whether the study should be terminated early due to futility or clear evidence of efficacy. The interim analysis will be conducted after half of the planned number patients have been enrolled. The Lan-DeMets method with an O’Brien and Fleming-type alpha spending function will be used to adjust the multiplicity of the interim analysis and the primary analysis [17].

JCOG Data Center staff will conduct central monitoring issuing a monitoring report twice annually to evaluate and improve study progress, data integrity and patient safety. Futility will be considered at each monitoring report if necessary. For quality assurance, site-visit audits, not for a study-specific basis but for the study group basis, will be performed by the JCOG Audit Committee.

## Discussion

Reducing the treatment burden while maintaining efficacy is important for elderly patients with newly diagnosed glioblastoma, which shows poor prognosis. The disadvantages of the standard treatment are prolonged gastrointestinal symptoms caused by temozolomide, prolonged hospitalization for about 2 months, and deterioration of QOL due to hospitalization. This study therefore plans to confirm whether hypofractionated radiotherapy requiring a shorter treatment period with temozolomide can overcome the disadvantages of standard treatment without compromising efficacy.

Based on the CE.6 trial results, the regimen of radiotherapy comprising 40 Gy in 15 fractions plus temozolomide is the standard treatment for newly diagnosed glioblastoma patients 65 years old or older. In actual clinical practice, however, elderly patients with satisfactory performance status, particularly those under 75 years old, tend to be treated with 60 Gy of radiotherapy in 30 fractions plus concomitant and adjuvant temozolomide. Our other phase III trial, JCOG1703, began in June 2019 and is currently recruiting patients under 75 years old with newly diagnosed glioblastoma to confirm the superiority of maximal resection with carmustine wafer implantation followed by chemoradiotherapy with temozolomide over maximal resection followed by chemoradiotherapy with temozolomide, at least in terms of OS [18]. As the definition of maximal tumor resection is resection exceeding 90%, patients with 71–75 years and resection of less than 90% of the contrast-enhanced region has been set as an inclusion criterion for this study.

*MGMT* is a DNA repair enzyme that confers chemoresistance to alkylating agents [19]. Promoter methylation of *MGMT* reflects epigenetic silencing associated with longer survival in patients with glioblastoma treated using alkylating agents. In the analysis of the CE.3 trial, patients with a methylated *MGMT* promoter showed a survival benefit from temozolomide (median OS, 21.7 months vs. 15.3 months), whereas those with an unmethylated *MGMT* promoter did not (median OS, 12.7 months vs. 11.8 months) [20]. Furthermore, *MGMT* promoter methylation represents an independent favorable prognostic factor irrespective of treatment. The CE.6 trial showed a similar result that patients with a methylated *MGMT* promoter achieved significantly prolonged survival with temozolomide (median OS, 13.5 months with radiotherapy plus temozolomide vs. 7.7 months with radiotherapy alone) and those with unmethylated *MGMT* promoter benefited slightly from temozolomide (median OS, 10.0 months with radiotherapy plus temozolomide vs. 7.9 months with radiotherapy alone) [10], which may suggest that short-course radiotherapy increases the efficacy of temozolomide in glioblastomas with unmethylated *MGMT* promoter.

Radiotherapeutic regimens of 40 Gy in 15 fractions, 34 Gy in 10 fractions, and 25 Gy in 5 fractions have been shown to offer similar efficacy and safety for elderly patients with glioblastoma according to the three earlier phase III studies [11–13]. The current task is to determine the optimal dose and number of fractions, particularly in combination with temozolomide, for elderly patients with newly diagnosed glioblastoma. The linear-quadratic (LQ) model has been used for predicting radiobiological response [21]. Equivalent-dose fractionation can be estimated by calculating equivalent doses in 2-Gy fractions (EQD2) on the LQ model. Although several studies have shown that the α/β values of glioma and normal brain tissue were 5–10 Gy and 2–3 Gy, respectively [22–24], and the α/β value of glioblastoma in elderly patients is estimated as less than 1.2 Gy from the results of recent clinical trials [10, 12, 13](Table 2). On the basis of the estimated α/β value 1.2 Gy, EQD2s of 40 Gy in 15 fractions and 25 Gy in 5 fractions were considered equivalent for glioblastoma in elderly patients, suggesting similar efficacy. Meanwhile, the EQD2 of 25 Gy in 5 fractions is less than that of 40 Gy in 15 fractions for normal brain tissue, meaning less damage would be incurred by 25 Gy in 5 fractions. These estimates are supported by study results finding no differences in OS, PFS, or QOL between patients receiving the two radiotherapy regimens of 40 Gy in 15 fractions and 25 Gy in 5 fractions [13].

**Table 2 Tab2:** Equivalent dose in 2-Gy fractions (EQD2) estimated on the LQ model

		α/β value			
Clinical trials	Radiation dose/fractions	1.2	3.0	5.6	10.0
Conventional radiotherapy	60 Gy/30 fr	60.0	60.0	60.0	60.0
Perry et al., 2017 [10], CE.6	40 Gy/15 fr	48.4	45.4	43.6	42.3
Roa et al., 2015 [13]	25 Gy/5 fr	48.4	40.0	34.9	31.3
Malmström et al., 2012 [12], Nordic study	34 Gy/10 fr	48.9	43.5	40.3	38.0

As concomitant treatment in the standard treatment, temozolomide is administered at 75 mg/m^2^ for 21 days, resulting in a total dose of 1575 mg/m^2^. On the other hand, if temozolomide at 75 mg/m^2^ is adopted as the concomitant treatment, the total dose of temozolomide is considerably reduced to 375 mg/m^2^ in 5 days and treatment intensity may thus be insufficient. Administration of temozolomide at 150 mg/m^2^ for 5 days has been confirmed as safe and effective as the first administration of maintenance treatment in the previous report [25]. In the study treatment, a synergistic effect is expected because both the single dose of temozolomide and radiation are increased, and maintenance treatment is implemented 2 weeks earlier than that in the standard treatment, so that the efficacy of temozolomide treatment is considered to be enhanced. According to the above, temozolomide at 150 mg/m^2^/day administered for 5 days was adopted as concomitant treatment for the study treatment.

Based on the prediction of radiobiological response from the results of clinical trials, the aim of this study is to confirm the non-inferiority of radiotherapy comprising 25 Gy in 5 fractions with concomitant and adjuvant temozolomide over 40 Gy in 15 fractions with concomitant and adjuvant temozolomide in terms of OS among elderly patients with newly diagnosed glioblastoma. If the primary endpoint is met, radiotherapy as 25 Gy in 5 fractions with concomitant and adjuvant temozolomide will be established as a standard of care for elderly patients with newly diagnosed glioblastoma. Furthermore, the α/β value of glioblastoma in elderly patients will be confirmed as less than 1.2 Gy. This study is designed as a multi-institutional, randomized controlled trial with a non-inferiority margin of 1.32, considering the disease rarity.

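### Meeting the overall-survival non-inferiority endpoint would not confirm an α/β value below 1.2 Gy, as the Discussion says it will

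*Protocol article*

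**What the plan says.** The last paragraph of the Discussion states what a positive trial will mean. First, if the primary endpoint is met, arm B's regimen is to become a standard treatment in this population. The next sentence reads "Furthermore, the α/β value of glioblastoma in elderly patients will be confirmed as less than 1.2 Gy". It continues from the same condition and carries no hedge.

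The 1.2 Gy figure comes from earlier in the Discussion. There, on the linear-quadratic model and at an estimated α/β of 1.2 Gy, "EQD2s of 40 Gy in 15 fractions and 25 Gy in 5 fractions were considered equivalent for glioblastoma in elderly patients" (Table 2). The same paragraph cites other studies that put the glioma value at 5–10 Gy.

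The only primary test described is non-inferiority of overall survival, with "a non-inferiority margin of 1.32 using a one-sided alpha of 0.05 to observe 249 deaths" (Statistical analysis). The Discussion justifies the margin by the rarity of the disease. No analysis that estimates or tests α/β is described.

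The arms differ in more than fractionation. In the standard arm, "temozolomide is administered at 75 mg/m^2^ for 21 days, resulting in a total dose of 1575 mg/m^2". Arm B receives "temozolomide (150 mg/m^2^, 5 days from first day" of radiation. The Discussion expects synergy in arm B, notes that maintenance begins 2 weeks earlier there, and concludes that temozolomide efficacy should be enhanced.

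**The concern.** The sentence turns a comparison of two whole regimens into proof about a radiobiological constant. Two steps in that inference fail.

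- **The test does not address the inequality.** On the article's own model, α/β below 1.2 Gy means that arm B delivers at least as much effective tumour dose as arm A. A non-inferiority test is built to tolerate some loss in arm B, so passing it does not show this.
- **Fractionation is not isolated.** Concomitant temozolomide dose, duration and total differ by arm, as does the start of maintenance. Similar survival could come from the drug schedule offsetting a weaker radiation schedule, or from other combinations of the two effects.

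What is at stake is what the trial may conclude. The α/β value is disputed within the article itself (1.2 Gy against 5–10 Gy), and a positive result would be credited with settling a question that the trial does not identify.

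**Working it through.** **Inputs.** Margin 1.32, one-sided alpha 0.05, power 70%, 249 deaths, 1-year survival 37.8% in both arms (Statistical analysis); 1:1 allocation (Randomization); schedules (Interventions); EQD2 values (Table 2); temozolomide totals and timing (Discussion).

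**1. Reproduce the design.** ln 1.32 = 0.2776; z-values 1.645 and 0.524.
- Schoenfeld: 4 × (1.645 + 0.524)² / 0.2776² gives 245 deaths after rounding up.
- Freedman: (1.645 + 0.524)² × (2.32 / 0.32)² gives 248.
- The stated 249 agrees closely. Power at 249 deaths is 70.7%, against the stated 70%.

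**2. Reproduce Table 2.** EQD2 = D(d + α/β) / (2 + α/β), with 15 × 2.67 = 40.05 Gy for arm A.

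| α/β (Gy) | 40 Gy/15 | 25 Gy/5 | Ratio B/A |
|---|---|---|---|
| 1.2 | 48.4 | 48.4 | 1.00 |
| 3.0 | 45.4 | 40.0 | 0.88 |
| 5.6 | 43.6 | 34.9 | 0.80 |
| 10.0 | 42.3 | 31.3 | 0.74 |

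Setting the two EQD2 values equal gives α/β = (125 − 40.05 × 2.67) / (40.05 − 25) = 18.07 / 15.05 = 1.20 Gy. With exactly 40 Gy it is (125 − 106.67) / 15 = 1.22 Gy. Below this point arm B has the higher EQD2, and above it the lower. Exactly equal radiation effect would therefore point to about 1.2 Gy, the boundary of the claimed range.

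**3. What a positive test shows.** SE(log HR) = 2/√249 = 0.127.
- Largest observed hazard ratio that passes: exp(0.2776 − 1.645 × 0.127) = 1.07, against arm B.
- Probability of passing at a given true hazard ratio is Φ[(ln 1.32 − ln HR)/0.127 − 1.645]:

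| True HR | P(non-inferiority declared) |
|---|---|
| 1.00 | 0.71 |
| 1.10 | 0.42 |
| 1.15 | 0.29 |
| 1.20 | 0.19 |
| 1.32 | 0.05 |

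These figures ignore the adjustment for the planned interim analysis. The hazard ratio at the margin corresponds to 1-year survival of 0.378^1.32 = 27.7%, against 37.8%.

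**4. Temozolomide contrast.** Arm A: 75 × 21 = 1575 mg/m². Arm B: 150 × 5 = 750 mg/m², which is 48% of arm A's total. Arm B's daily dose is twice as high (150 vs 75 mg/m²) and its maintenance starts 2 weeks earlier. The net direction of these differences on survival is unknown.

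**The case against.** The strongest reply is that nothing in the trial depends on this sentence. The aim, endpoints, sample size and primary analysis do not mention α/β, and the abstract's conclusion claims only a standard of care. The whole regimen, radiotherapy with temozolomide, is the unit compared throughout, and the temozolomide differences are set out openly just above the sentence. The Discussion also already offers a value below 1.2 Gy as an estimate from earlier trials, so the sentence may be a loose echo of that, with 1.2 a rounded figure. All of this stands as to weight: it makes the point minor and one of interpretation. It does not rescue the claim that a positive result will confirm the value.

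Some stronger readings are tempting but not supported:

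- **That an arm worse by a hazard ratio of 1.32 passes easily.** At that true value the test passes only 5% of the time. The sound statement concerns modest losses, such as 0.42 at 1.10.
- **That a stated shortfall in EQD2, such as the 12% at α/β = 3 Gy, would pass.** The ratio is correct, but turning it into a hazard ratio needs a dose-response slope that the article does not give. No bound on α/β follows from excluding 1.32.
- **That the temozolomide difference favours arm B.** The total is lower and the daily dose higher, so the direction is open.
- **That the trial report will repeat the claim.** That would be a prediction about a later document.

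**Conclusion.** The statement is unsupported as written. A positive result can occur with an observed hazard ratio up to about 1.07 against arm B, and with probability about 0.42 at a true hazard ratio of 1.10, whereas the claimed inequality requires arm B's radiation to be at least as effective as arm A's. Independently of that, the different temozolomide exposure (1575 vs 750 mg/m²) and the earlier maintenance mean that even equal or better survival in arm B would not identify α/β.

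The first argument rests on the article's linear-quadratic model, proportional hazards, 249 deaths with 1:1 allocation, and no interim adjustment. The second needs only the treatment descriptions. Neither shows that α/β is above 1.2 Gy; the trial simply does not decide the question. Severity is minor, and the non-inferiority design and its figures stand.

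**What to change.** Delete the sentence, or replace it with wording such as: *A positive result applies to the two chemoradiotherapy regimens as given. It would be compatible with a low α/β ratio but would not confirm one, because temozolomide dose and timing also differ between the arms.* If an α/β estimate is to be reported, label it exploratory, state the assumptions that link dose to survival, and give it with an interval.

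The cost is one sentence and a more modest stated conclusion. Sample size, alpha, the primary analysis and trial conduct do not change.
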